# Appendix E: Pharmacokinetic (PK) Evaluations

**SCHEMA**

**Genetic Predictors of Raltegravir Penetration into Cerebrospinal Fluid**

DESIGN: This single arm, open-label healthy volunteer study will determine whether there are associations between a frequent C>T single nucleotide polymorphism (SNP) at position 3435 (rs1045642) in the drug transporter gene *ABCB1* (also known as *MDR1*) and penetration of raltegravir (RGV) into cerebrospinal fluid (CSF). Study participants will take RGV 400 mg orally every 12 hours for 7 days. On Day 7 of RGV participants will undergo 24-hour serial plasma sampling to determine steady-state plasma pharmacokinetic (PK) parameters for RGV. A plasma sample will also be obtained on Day 9. Peripheral blood mononuclear cells (PBMCs) will be obtained to measure intracellular RGV. Lumbar puncture will be performed 4 hours after the morning dose on Day 7 to quantify the CSF RGV concentration. Primary outcomes of interest will be ratios of the CSF RGV C4h value to the plasma RGV Cmax, Cmin and AUC0-12h values.

DURATION: Subject’s participation may last as many as 12 months, but in most cases approximately 3 month.

SAMPLE SIZE: This study will enroll 40 subjects over approximately 2 year.

POPULATION: Healthy, HIV-negative volunteers who are at least 18 years of age, with body mass index less than 30, and with acceptable screening laboratories. Only individuals of self-reported white European ancestry, and whose parents’ were both of white European ancestry may participate. With regard to *ABCB1* 3435 C>T, the study will include 20 C/C homozygotes and 20 T/T homozygotes. Each genotype group will comprise 10 males and 10 females, as follows:

|  | *ABCB1* 3435 genotype | |
| --- | --- | --- |
|  | C/C | T/T |
| Male | 10 | 10 |
| Female | 10 | 10 |

RANDOMIZATION: None

REGIMEN: Study participants will receive RGV 400 mg orally every 12 hours for 7 days.

1. **Background**

Many antiretroviral drugs are substrates for P-glycoprotein (P-gp) [1-6]. This multidrug efflux transporter is expressed in the blood-brain barrier where it limits entry of substrate drugs into the central nervous system (CNS) [3]. Emerging data support the potential relevance of CNS drug penetration in at least some individuals [7]. Raltegravir (MK-0518) is a substrate for P-gp based on its directional transport in the well-established LLC-PK1 cell culture model. Preclinical data also indicate low brain-to-plasma concentration ratios for RGV. Further studies are warranted to elucidate the relevance of P-gp transport for RGV in the CNS.

Raltegravir has a low likelihood of drug-drug pharmacokinetic interactions (Isentress Prescribing Information, 5/2008). Raltegravir does not inhibit CYP1A2, CYP2B6, CYP2C8, CYP2C9, CYP2C19, CYP2D6 or CYP3A *in vitro*. Moreover, *in vitro*, raltegravir did not induce CYP3A4. A midazolam drug interaction study confirmed the low propensity of raltegravir to alter the pharmacokinetics of agents metabolized by CYP3A4 *in vivo* by demonstrating a lack of effect of raltegravir on the pharmacokinetics of midazolam, a sensitive CYP3A4 substrate. Similarly, raltegravir is not an inhibitor of the UDP glucuronosyltransferases (UGT) tested (UGT1A1, UGT2B7), and raltegravir does not inhibit P-glycoprotein-mediated transport. Based on these data, raltegravir is not expected to affect the pharmacokinetics of drugs that are substrates of these enzymes or P-glycoprotein. Raltegravir is not a substrate of cytochrome P450 (CYP) enzymes. Based on *in vivo* and *in vitro* studies, raltegravir is eliminated mainly by metabolism via a UGT1A1-mediated glucuronidation pathway.Rifampin, a strong inducer of UGT1A1, reduces plasma concentrations of raltegravir. Therefore,caution should be used when coadministering raltegravir with rifampin or other strong inducers ofUGT1A1.Other less strong inducers may be used with the recommended dose ofraltegravir. Atazanavir, a strong inhibitor of UGT1A1, and atazanavir/ritonavir increase plasma concentrations of raltegravir. However, concomitant use of raltegravir and atazanavir/ritonavir did not result in a unique safety signal in Protocol 005 and Protocols 018 and 019. Based on these data, atazanavir/ritonavir may be coadministered with raltegravir without dose adjustment of raltegravir. Coadministration of raltegravir with other drugs that inhibit UGT1A1 may increase plasma levels of raltegravir.

P-glycoprotein is encoded by *ABCB1* (previously called *MDR1*). *ABCB1* is highly polymorphic, and a frequent *ABCB1* polymorphism (3435C>T; rs1045642) has been associated with decreased P-glycoprotein activity in numerous studies [8,9]. This polymorphism is present in approximately 50% of European Americans and 17% of African Americans [10]. A number of studies (including several from our group) have suggested associations between *ABCB1* 3435C>Tandresponses to HIV therapy [10-14], although study results are somewhat conflicting. Some studies also suggest that another *ABCB1* polymorphism (2677G>T/A; rs2032582) which is in incomplete linkage with 3435C>T may also be associated with altered P-glycoprotein activity, although results have also been conflicting [8].

Important aspects regarding the PK of RGV have yet to be defined. Because the target of RGV is intracellular, prolonged intracellular exposure with RGV may help explain its efficacy, but the terminal elimination PK of RGV from within PBMCs among individuals who have been dosed to steady-state have not been defined. Similarly, the terminal elimination PK of RGV from plasma among individuals who have been dosed to steady-state have not been defined.

Our group has devoted considerable effort to elucidating the relevance of human genetic variability for antiretroviral drug disposition, efficacy, and toxicity [10,12-20]. The proposing investigator also has considerable experience studying HIV disease in the CNS, including pharmacokinetics of drug penetration into CSF [21-26]. The present proposal extends this work to RGV, a major addition to our therapeutic armamentarium.

1. **Rationale and Specific Aims**

Our hypothesis is that a frequent *ABCB1* single nucleotide polymorphism (SNP) influences disposition of RGV into the CNS, which may in turn be relevant for HIV treatment response in this compartment.

**SPECIFIC AIMS:**

2.0.1 **Primary aim**

1. To determine whether *ABCB1* 3435C>T is associated with altered cerebrospinal fluid (CSF)-to-plasma RGV concentration ratios among healthy volunteers at steady state.

2.0.2 **Secondary aims**

1. To determine whether *ABCB1* 2677G>T and/or other *ABCB1* SNPs are associated with altered CSF-to-plasma RGV concentration ratios among healthy volunteers at steady state.

2. To characterize PBMC intracellular pharmacokinetics of RGV at steady state, and associations with *ABCB1* 3435C>T and 2677G>T.

3. To characterize plasma terminal elimination pharmacokinetics of RGV, and associations with *ABCB1* 3435C>T and 2677G>T.

4. To store leftover DNA, plasma and CSF specimens that may be used for future unplanned analyses of RGV and/or its metabolites, and of additional human DNA polymorphisms.

1. **Animal Studies and Previous Human Studies**

See Investigator Brochure for Raltegravir (MK-0518).

1. **Inclusion/Exclusion Criteria**

4.0.1 **Study participants**

The study will enroll 40 healthy volunteers. Of these 40 individuals, 20 will be *ABCB1* position 3435 C/C homozygotes, and 20 will be 3435 T/T homozygotes. Each of the two genotype groups we comprise 10 males and 10 females. There will therefore be 4 separate groups.

4.0.2 **Inclusion Criteria**

1. Able and willing to give written informed consent.

2. Negative HIV-1 serology documented by any licensed ELISA test kit within 30 days prior to initiating study drug.

3. Men and women at least 18 but no more than 55 years of age at study entry.

4. Body mass index less than 30.

Body mass index = (weight in kilograms)/(height in meters)2

OR

Body mass index = [(weight in pounds)/(height in inches)2] X 703

5. Estimated creatinine clearance ≥ 50 mL/minute within 30 days prior to study entry, calculated by the Cockcroft-Gault method as follows:

Men: creatinine clearance = [(140 - age) x (weight in kg)]/(72 x serum creatinine)

Women: creatinine clearance = 0.85 x [(140 - age) x (weight in kg)]/(72 x serum creatinine)

6. Laboratory values obtained within 30 days prior to study entry:

- Absolute neutrophil count (ANC) ≥ 1,000/mm3.
- Hemoglobin  12.5 g/dL for males and  11.5 g/dL for females.
- Platelet count  100,000/mm3.
- AST (SGOT), ALT (SGPT), and total bilirubin within normal range.
- Alkaline phosphatase  1.5  upper limit of normal (ULN).

7. Female study volunteers of reproductive potential (defined as women who have not been post-menopausal for at least 24 consecutive months, i.e., who have had menses within the preceding 24 months, or have not undergone surgical steriliza­tion [e.g., hysterectomy, bilateral oophorectomy, or salpingotomy]) must have a negative serum or urine pregnancy test performed within 30 days before study entry.

8. All study volunteers must agree not to participate in a conception process (e.g., active attempt to become pregnant or to impregnate, sperm donation, in vitro fertilization).

If participating in sexual activity that could lead to pregnancy, all study volunteers must agree that AT LEAST ONE of the following reliable methods of contraception will be used while they are receiving protocol-specified medications and for 6 weeks after stopping the medications:

- Condoms1 (male or female) with or without a spermicidal agent
- Diaphragm or cervical cap with spermicide
- IUD

1 Condoms are recommended because their appropriate use is the only contraception method effective for preventing HIV transmission.

NOTE: Use of hormonal contraceptives is prohibited during this study because of the potential for drug interactions.

All study volunteers who are not of reproductive potential (e.g., women who have been post-menopausal for at least 24 consecutive months, or women who have undergone surgical sterilization [e.g., hysterectomy and/or bilateral oophorectomy or salpingotomy], or men who have documented azoospermia) are eligible without requiring the use of contraception. Acceptable documentation of sterilization or menopause consists of written or oral documentation communicated by a clinician or a clinician’s staff of one of the following:

- - - - Physician report/letter
      - Operative report or other source documentation in the patient record (a laboratory report of azoospermia is required to document successful vasectomy)
      - Discharge summary
      - Laboratory report of azoospermia
      - FSH measurement elevated into the menopausal range as established by the reporting laboratory.

9. Drug transporter gene *ABCB1* position 3435 genotype either homozygous C/C or homozygous T/T.

10. Self-reported white (of European ancestry), AND both parents of white European ancestry.a

a NOTE: Because *ABCB1* T/T genotype is relatively infrequent among individuals of African decent, it is not feasible to perform this study in such individuals because screening would require an extremely large number of individuals. However, if associations are found in this study, future studies may extend to other populations.

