**6.0.4 Summary of study events by day**

"Day 1" is the day that study drug is first administered.

Days -365 to -1

1. Obtain written informed consent

2. Venipuncture to obtain blood sample for *ABCB1* genotype.

NOTE: The -365 day window is intended to allow flexibility so that *ABCB1* genotype assays can be batched to increase genotyping efficiency and to accommodate subjects’ schedules. The actual time interval from consenting to Day 1 will be far less than 90 days in most participants.

Days -30 to -1

1. Venipuncture to obtain blood sample for screening safety lab tests, HIV serology.

2. History and physical examination.

3. Neurological examination.

4. Routine screening laboratory assay.

4. Urine pregnancy test (Women only. Must have negative test before taking study medications).

Day 1

1. Urine or Serum pregnancy test (Women only. Must have negative test before beginning study drug).

2. Provide participant with medication diary to document timing of every dose of RGV.

3. Begin RGV 400 mg orally every 12 hours. The first dose is at time specified by study personnel on Day 1.

Days 2-6

1. Continue RGV 400 mg orally every 12 hours in the AM and in the PM, as instructed.

Day 6

1. Arrive at VICTR-CRC in evening, at time specified.

2. Venipuncture to obtain blood sample for safety lab tests.

3. Provide snack 30min. prior to study drug administration.

4. Collect medication diary from participant, and assess adherence.

5. Continue RGV 400 mg orally every 12 hours. The scheduled PM dose of RGV 400 mg should be observed by VICTR-CRC staff and documented.

6. Leave the VICTR-CRC after taking the observed dose of RGV

NOTE: Under rare circumstances the participant may stay in the VICTR-CRC overnight on Day 6.

NOTE: Participant needs to be fasting 8 hours before the final scheduled AM dose of RGV. Only water and coffee with no cream or sugar are allowed.

Day 7

1. Arrive at VICTR-CRC at 6 AM. Admit as inpatient.

2. Day 6 lab results reviewed.

3. Fasting is required for an additional 3 hours after final dose of RVG. Water and coffee with no cream or sugar are allowed. A light regular meal will be given 3 hours after final dose of RVG.

4. Consent form re-signed for LP.

5. Place an indwelling venous catheter in a peripheral arm vein.

6. Serial plasma and PBMC sampling for RGV PK.

NOTE: See Appendix for timing and processing of plasma and PBMC samples.

7. Lumbar puncture 4 hours after the morning RGV dose.

Day 8

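### Inclusion items 7 and 8 list salpingotomy as surgical sterilisation, so a woman still able to conceive could be exempted from contraception

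*Protocol*

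**What the plan says.** Section 4.0.2 uses reproductive potential for two purposes.

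- **Item 7 (pregnancy test at entry).** Women of reproductive potential are "defined as women who have not been post-menopausal for at least 24 consecutive months", explained as those "who have had menses within the preceding 24 months, or have not undergone surgical" sterilisation. The examples and the consequence follow: "hysterectomy, bilateral oophorectomy, or salpingotomy]) must have a negative serum or urine pregnancy test performed within 30 days before study entry".
- **Item 8 (contraception).** It opens with a rule for everyone: "All study volunteers must agree not to participate in a conception process". Volunteers whose sexual activity could lead to pregnancy must use at least one listed barrier method or an IUD while on study drug and for 6 weeks afterwards. Hormonal contraceptives are prohibited. Those not of reproductive potential are excused. For women this means "women who have been post-menopausal for at least 24 consecutive months, or women who have undergone surgical sterilization", and the examples and consequence are: "hysterectomy and/or bilateral oophorectomy or salpingotomy], or men who have documented azoospermia) are eligible without requiring the use of contraception".
- **Item 8 (proof).** "Acceptable documentation of sterilization or menopause consists of written or oral documentation communicated by a clinician or a clinician’s staff"; an operative report is one of the accepted forms. For vasectomy, a laboratory report of azoospermia is required.

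Section 6.0.4 lists a pregnancy test for women in the 30 days before Day 1 and again on Day 1: "Urine or Serum pregnancy test (Women only. Must have negative test before beginning study drug". Appendix A shows the same two time points and none later. Neither place limits the test to women of reproductive potential.

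**The concern.** The exemption in item 8 is meant for people who cannot conceive or father a child. Its example list includes a procedure that, on the ordinary meaning of the word, does not end fertility. An example in an eligibility criterion tells site staff what qualifies. A woman with an accurate record of a salpingotomy could therefore be classed as sterilised and take the study drug without the contraception that the protocol asks of other fertile participants. The matter is one of participant protection. It does not bear on the estimate or the test of the genotype effect.

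Items 7 and 8 also do not define reproductive potential in the same way. That calls for a separate check on whether the mismatch changes how anyone is handled.

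**Working it through.** The protocol gives no figure to reproduce here, so the check compares texts, with a small truth table.

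**1. The term.** The protocol does not define salpingotomy. In ordinary medical vocabulary the ending -otomy denotes an incision and -ectomy a removal. The same lists use -ectomy for the uterus and the ovaries, so the wording itself observes the distinction. It is unclear whether the adjective bilateral carries over from oophorectomy, but this does not matter: incisions on both sides also leave both tubes in place.

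**2. From the term to the exemption.** A listed procedure counts as surgical sterilisation, which counts as not being of reproductive potential, which removes the contraception requirement. An operative report or an oral statement from a clinician's staff is accepted as proof. For vasectomy the protocol asks for laboratory evidence of the result; for women the record of the procedure is enough.

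**3. What remains for a woman exempted in this way.**
- The required period is 7 days of drug plus 6 weeks: 7 + 42 = 49 days, or 7 weeks.
- Pregnancy tests fall at screening and on Day 1. They detect an existing pregnancy and cannot prevent a later one.
- The last scheduled contact is by telephone or email on Day 14 (± 2 days), so Day 16 at the latest. Counting 6 weeks from Day 7, the period ends on Day 49, which is 49 − 16 = 33 days or more after that contact.
- The agreement not to take part in conception still binds her. Its examples are deliberate acts: trying to conceive, sperm donation, in vitro fertilisation. Unintended pregnancy is dealt with by the contraception clause, which is the part that is lifted.
- The ban on hormonal contraceptives applies during the study, so she need not use a listed method and may not use a hormonal one.

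**4. The two definitions.** Let A = post-menopausal for at least 24 months and B = surgically sterilised. Item 7, read literally: of potential = (not A) or (not B). Item 8: not of potential = A or B.

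| A | B | Item 7, literal | Item 8 | Agree? |
|---|---|---|---|---|
| no | no | of potential | of potential | yes |
| yes | no | of potential | not of potential | no |
| no | yes | of potential | not of potential | no |
| yes | yes | not of potential | not of potential | yes |

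Two of the four states conflict. If item 7 is read as neither post-menopausal nor sterilised, which is evidently the intent, none conflicts. Under either reading the women excused from contraception are those with A or B, because item 8 alone sets that group. Item 7 decides only who needs a pregnancy test, and section 6.0.4 and Appendix A test every woman in any case.

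**The case against.** The strongest reply is that the governing terms are reproductive potential and surgical sterilisation, and that the procedures are only examples. Proof must be of sterilisation or menopause, and a report of an operation that conserves the tube does not obviously prove either. A careful investigator would notice. In addition, every woman is tested before dosing, and the agreement against conception stays in force.

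Part of this stands. The safeguards are real, and an alert site might refuse the exemption. But a named example tells staff that the procedure qualifies, so the criterion should not depend on a reader overruling its own list. The remaining safeguards do not replace contraception against unintended pregnancy.

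Four stronger readings are tempting, and the protocol does not support them:

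- **That the conflict between items 7 and 8 is what lets a fertile woman be exempted.** It exempts no one. The loose wording of item 7 only widens the group to be tested, which is the protective direction.
- **That nothing else protects such a woman.** The agreement against conception and the two pregnancy tests apply to her.
- **That all 20 planned women are concerned.** Twenty is only the ceiling. The point applies to a woman who has had this operation, is still fertile, has sexual activity that could lead to pregnancy, and is classed as sterilised on that ground.
- **That the lumbar puncture adds to the problem.** It has no bearing on the exemption; the issue is exposure to study drug without contraception.

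**Conclusion.** The point holds for the term. Salpingotomy does not belong under the protocol's own heading of surgical sterilisation, and it stands in both items. In item 8 it has a consequence: a woman still able to conceive could be excused from contraception for about 7 weeks. This rests on the ordinary meaning of the word, since the protocol gives no definition, and on staff applying the list as written.

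The number affected is probably very small. The protocol gives no basis for estimating it, and it may be zero. Sample size, power and the primary comparison are unaffected.

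The mismatch between the two definitions is a drafting fault with no operational effect under the present testing schedule. The case for acting is that a protection the protocol itself imposes can be defeated by one word, and that correcting it costs almost nothing.

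**What to change.** Correct the term salpingotomy in items 7 and 8 so that the exemption list names only procedures that the sponsor has verified to be sterilising. Which procedures those are is for the sponsor to settle; this review proposes none. At the same time, reconcile the two items into one definition of reproductive potential, so that the women covered by item 7 are exactly those not excused by item 8.

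The cost is a wording change in two inclusion items, with no added visits, tests or participants. At most, an occasional woman would have to agree to one of the contraceptive methods already listed.

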## 4.0.3 Exclusion Criteria

1. Within 14 days prior to entry, use of any medication that is known to be a potent inducer (e.g. rifampin) or inhibitor (e.g. ritonavir) of CYP3A or UGT1A1 (refer to manufacturers’ package inserts for individual drugs).

2. Anticipated need to take any medication that is known to be a potent inducer or inhibitor of CYP3A or UGT1A1 during the study.

3. Active drug use or dependence that, in the opinion of the investigator, would interfere with adherence to study requirements.

4. Inability to abstain from alcohol-containing beverages, grapefruit, and grapefruit juice for the duration of the study.

5. Serious illness that, in the opinion of the investigator, would interfere with study participation.

6. Hospitalization for any reason or therapy for serious illness within 14 days prior to study entry.

7. History of hypersensitivity to study drug or its formulation.

8. As determined by the investigator, a significant active or previous history of cardiovascular, renal, liver, hematologic, neurologic, gastrointestinal, psychiatric, endocrine, or immunologic disease(s). This is inclusive of chronic illnesses such as hypertension, coronary artery disease, arthritis, diabetes, any chronic gastrointestinal conditions that may affect drug absorption, etc.

9. Breast-feeding.

10. Evidence of CNS infection or space occupying lesion by history or physical examination.

11. History of significant CNS disorder such as trauma, congenital malformations or genetic disorders.

12. Prisoners or subjects who are compulsorily detained (involuntarily incarcerated) for treatment of either a psychiatric or physical (e.g., infectious disease) illness must not be enrolled into this study.

13. *ABCB1* position 3435 C/T heterozygosity during screening evaluation.

1. **Enrollment/Randomization**

There is no randomization involved in this study. Subjects will be screened and registered for enrollment at the Vanderbilt AIDS Clinical Trials Center (ACTC).

Vanderbilt ACTC

[name]

[name]

[contact]

[contact]

Potential study participants will be recruited by word of mouth, by email advertisement through the Vanderbilt system and flyers that will be pre-approved by the Vanderbilt IRB.

ACTC research staff will give a copy of the consent form to potential participants, will discuss study procedures, risks and benefits of the study, and will obtain written informed consent. After signing the informed consent document, subjects will have blood drawn for screening laboratory tests.

1. **Study Procedures** (Refer to Appendix A for Schedule of Events)

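### The medication exclusions cover CYP3A and UGT1A1 but not P-glycoprotein, so P-gp modulators that are not also potent on those enzymes remain allowed in a trial of P-gp function

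*Protocol*

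**What the plan says.** Protocol section 2 gives the hypothesis that an ABCB1 polymorphism influences raltegravir's passage into the central nervous system. The primary aim tests ABCB1 3435C>T against CSF-to-plasma concentration ratios. The Background states that ABCB1 encodes P-gp, that P-gp restricts entry of its substrates at the blood-brain barrier, and that 3435C>T has been associated with lower P-gp activity. On the drug itself it says:

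- "Raltegravir (MK-0518) is a substrate for P-gp based on its directional transport in the well-established LLC-PK1 cell culture model"
- "Raltegravir is not a substrate of cytochrome P450 (CYP) enzymes"
- "raltegravir is eliminated mainly by metabolism via a UGT1A1-mediated glucuronidation pathway"

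Two exclusion criteria in section 4.0.3 deal with interacting drugs. Item 1 covers the 14 days before entry: "use of any medication that is known to be a potent inducer (e.g. rifampin) or inhibitor (e.g. ritonavir) of CYP3A or UGT1A1". Item 2 covers the study period: "Anticipated need to take any medication that is known to be a potent inducer or inhibitor of CYP3A or UGT1A1 during the study".

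The other limits on what participants may take are the ban on hormonal contraceptives (section 4.0.2, item 8), abstention from alcohol and grapefruit (section 4.0.3, item 4; Appendix E for grapefruit) and the exclusion of drug use that would interfere with adherence (section 4.0.3, item 3). Item 8 of section 4.0.3 excludes significant or chronic disease, which indirectly limits long-term medication. None of these names P-gp or ABCB1, and the protocol has no separate list of prohibited drugs.

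**The concern.** On the protocol's own hypothesis, a P-gp inhibitor would do by drug what the T/T genotype is expected to do by inheritance: lower P-gp function and let more raltegravir into the CSF. An inducer would do the reverse. A C/C participant on an inhibitor could then look like a T/T participant, which blurs the one contrast the trial is built to measure.

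The criteria protect plasma exposure through UGT1A1, the stated main elimination route. They also restrict CYP3A, for which the Background gives no role in raltegravir's metabolism. The transporter under test is left out. With 17 evaluable participants planned per genotype group, a few affected individuals could alter both the difference in means and the spread.

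**Working it through.** **1. Does any restriction close the gap?** Each medication or related restriction against P-gp:

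| Restriction | Where | Reaches P-gp? |
|---|---|---|
| Potent CYP3A or UGT1A1 modulators | 4.0.3, items 1 and 2 | Only drugs that also act potently on one of these enzymes |
| Hormonal contraceptives | 4.0.2, item 8 | Not by name |
| Alcohol, grapefruit | 4.0.3, item 4 | Not by name |
| Significant or chronic disease | 4.0.3, item 8 | Indirectly; lowers long-term drug use |
| Serious illness, or therapy for it within 14 days | 4.0.3, items 5 and 6 | Indirectly |

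What remains is a drug that modulates P-gp, is not potent on CYP3A or UGT1A1, and is taken by someone without excluded disease.

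**2. The plan's own sample size.** Inputs from section 10: difference 0.001, SD 0.001, alpha 0.05, Student's t test, 17 per group for 80% power. The standardised difference is 0.001/0.001 = 1. With n per group, the noncentrality is 1 × √(n/2) on 2n − 2 degrees of freedom. At n = 17 it is √8.5 = 2.92 on 32 degrees of freedom. Exact two-sided power is:

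- n = 16: 78.1%
- n = 17: 80.7%
- n = 20: 86.9%

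So 17 is the smallest group size that reaches 80%, and the stated figure reproduces.

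**3. Illustration A: affected participants shift up by 1 SD.** This size is an assumption. It equals the planned genotype difference, so an affected C/C participant moves to the T/T mean. If k of n C/C participants are affected, the true difference falls from 1 to 1 − k/n (at n = 17: 0.941 for one, 0.882 for two), and the C/C group also becomes more spread out. If equal numbers are affected in both groups, the difference stays at 1 and only the spread grows. If only T/T is affected, the difference rises to 1 + k/n. Power from simulated two-sample t tests:

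| Evaluable per group | Affected | Power |
|---|---|---|
| 17 | none | 81% |
| 17 | 1 C/C | 75% |
| 17 | 2 C/C | 68% |
| 17 | 1 in each group | 79% |
| 17 | 2 in each group | 78% |
| 17 | 1 T/T only | 84% |
| 20 | none | 87% |
| 20 | 1 C/C | 83% |
| 20 | 2 C/C | 78% |

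**4. Illustration B: the drug abolishes the genotype difference.** Suppose k of 17 in each group are affected and the SD stays at 0.001. The difference is 1 − k/17 and the noncentrality is (1 − k/17) × 2.92:

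- k = 1: 0.941 × 2.92 = 2.74, power 75.8%
- k = 2: 0.882 × 2.92 = 2.57, power 70.4%

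Neither k nor the size of the shift can be taken from the protocol. The tables show how power responds to assumed values; they do not predict a loss.

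**The case against.** The strongest reply is that the gap is narrow. P-gp modulators that are also potent on CYP3A or UGT1A1 are already barred. Participants are healthy, aged 18 to 55, free of significant or chronic disease, and dosed for 7 days. What is left is mainly incidental short-term use, and no frequency is documented. This stands, and it limits the weight of the point. It does not remove it, because short-term use needs no chronic illness and nothing prohibits it.

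A reader might infer that P-gp drugs in general are permitted. The text does not support that, because of the overlap just described.

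A reader might also infer a large loss of power. Placing two affected participants in C/C with a 2 SD shift gives 50% at 17 per group, and one gives 66%. Those figures need every affected participant to be C/C, and a shift that carries them a full SD past the T/T mean. Nothing in the protocol ties co-medication to genotype, and the mechanism goes no further than making C/C resemble T/T. With use in both groups at 1 SD the loss is two or three points, and use in T/T alone raises power. At 20 evaluable per group, one affected C/C participant still leaves power above 80%. Section 10 itself calls the power calculation a rough estimate.

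Nor does it follow that the CYP3A wording should go. It still removes any drug that acts on both CYP3A and P-gp.

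**Conclusion.** The point holds as a limited eligibility gap. Items 1 and 2 of section 4.0.3 omit the transporter whose gene is under test, and no other provision supplies it. The protocol's own pharmacology makes a P-gp modulator a direct disturbance of the primary contrast.

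The size is uncertain and probably small in this population. Across the illustrations, one or two affected participants (in one group or in each) move power from 81% to between 68% and 84% at 17 per group. At 20 per group, one or two affected C/C participants move it from 87% to 83% or 78%. These figures rest on the section 10 assumptions (normal data, SD and difference both 0.001, two-sided alpha 0.05) and on assumed numbers affected and effect sizes. The protocol does not show that the trial is biased or underpowered for this reason. The case for acting is that the correction is specific and nearly free.

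**What to change.** In section 4.0.3, extend items 1 and 2 so that they refer to CYP3A, UGT1A1 or P-glycoprotein. Which drugs this covers, and whether the 14-day window suits them, is for the sponsor to settle.

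The cost is a short change to two criteria and slightly fewer eligible volunteers. That loss should be small because chronic disease is already excluded.

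For anyone enrolled before the change, P-gp-active co-medication could be identified and the primary comparison repeated without those participants. This is secondary. Appendix A lists no collection of concomitant medication, so records would have to be obtained, and such a sensitivity analysis may already sit in a statistical analysis plan that was not available here.
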